## 5.5. Sensitivity analysis

The secondary endpoints evaluating changes in (MADRS, MADR-S, SDS, and CGI) score during different/several time points will be conducted by using MMRM models, fitting treatment, timepoint, and a treatment\*timepoint interaction. The models will be built as of the primary endpoint (see 5.4 Primary analysis). Paired t-test will be performed for between-groups comparisons at all time points, and between all time points over time against baseline. Response will be defined as  $\geq 50\%$  decrease (MADRS and MADR-S) compared to the last measurement before dosing, and remission will be defined as a (MADRS and MADR-S) score  $\leq 10$ . In addition, response will also be defined as  $> 10$  points decrease (MADRS and MADR-S) compared to the last measurement before dosing. Response and remission rate at all time points post dose will be analyzed by using Fisher's exact test and univariable logistic regression with odds ratios (OR) and their 95% confidence intervals (CI) and nominal p-values. An additional secondary endpoint will be time to initiation of antidepressant treatment. Time to initiation of antidepressant will be defined as the time (in days) from day 43 to the date when any antidepressant has been prescribed. Subjects will be censored at study discontinuation or completion. The Kaplan-Meier approach will be assessed with the log-rank test.

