#### **5.5.1.1 MADRS self-rating (MADRS-S)**

In order to get preliminary information on time to response and remission, duration of clinical effect, the self-rating version of MADRS will be administered at web-screening, PET1, day 0 prior to dosing, and day 1-8, 15 and monthly from day 42, 180 and 365 electronically via the participants smart phone or computer at the site as implemented the Region Stockholm web based patient interface 1177.se.

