#### **5.5.2 Sheehan Disability Scale (SDS)**

The SDS will be utilized to determine the impact of psilocybin vs. placebo on functional disability (psychosocial functioning). This will be a key secondary endpoint for the current study. The SDS is a composite of three self-rated items designed to measure the extent to which three major sectors in the patient's life are impaired by psychiatric symptoms, including depression. This scale has been used widely in psychopharmacology randomized controlled trials and has been accepted by the Food and Drug Administration (FDA) for functional disability labeling. The SDS uses visual-spatial, numeric, and verbal descriptive anchors simultaneously to assess disability across three domains: work, social life, and family life. The SDS was developed as an intervention outcome measure that would be sensitive to change and to drug placebo differences over time. The SDS asks patients to rate the extent to which his or her 1) work/school, 2) social life or leisure activities, and 3) home life or family responsibilities are impaired by his or her symptoms on a 10-point visual analog scale. There are verbal descriptors for the points on the scale as well as numerical scores that provide more precise levels of the verbal descriptors. Typically, four scores are derived from the scale in research studies – one for each of the work, social life and family life disability measures and an aggregate total score of these three scores combined.

SDS is a self-report instrument that will be collected electronically at day -3, 0, 8, 15, 42 and then monthly until 365, via the participants smart phone or computer as implemented the Region Stockholm web-based patient interface 1177.se.

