#### 16.4.1 Efficacy Analyses

The difference between psilocybin and placebo in change from baseline to Day 8 in MADRS total score (primary endpoint) will be analyzed for the Full Analysis Set using Analysis of Covariance including treatment as main effect and baseline as covariate. The same method will be applied for all other single measure endpoints. Treatment differences of multiple measurement endpoints will be analyzed by the mixed model repeated measurements analysis (MMRM) method.

Response and remission rate will be analyzed using logistic regression with the baseline measure as a covariate. The adjusted percentage with 95% CI, Odds Ratio with 95% CI and nominal p-values for the treatment comparison will be presented.

Time to initiation of antidepressant will be defined as the time (in days) from day 43 to the date when any antidepressant has been prescribed. Kaplan-Meier plots of time to initiation of antidepressant will be displayed by treatment groups. Time to initiation of antidepressant will be censored at study discontinuation or completion.

If the assumption of normality does not hold for a particular endpoint on the original scale of measurement, nonparametric methods (e.g. Mann Whitney U test, Fisher's exact) or common transformations (e.g., ln, sqrt) of the original data may be used.

P-values less than 0.05 will be considered statistically significant. As default all tests will be two-sided and two-sided 95% confidence intervals will be computed for the treatment difference. However, any hypothesis that includes a direction of change, eg *increased* [11C]UCB-J binding after dosing, will be tested using one-sided test using a significance level of 0.025.

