### 5.4. Primary analysis

The primary endpoint is change from baseline to Day 8 in MADRS total score. The primary analysis will be a mixed-model repeated measures (MMRM) model, fitting treatment, timepoint, and a treatment\*timepoint interaction. An unstructured covariance matrix will be used to estimate the within subject variation and the Kenward-Roger approximation will be used to estimate denominator degrees of freedom. If this analysis fails to converge, the following structures will be used in order: heterogeneous Toeplitz (TOEPH), Antependence (ANTE1), heterogeneous autoregressive (ARH1), Autoregressive (AR1) and Compound symmetry (CS). The first covariance structure yielding convergence will be used. If a structured covariance is used, the empirical "sandwich" estimator of the standard error (SE) of the fixed effects parameters will be used to deal with possible model misspecification of the covariance matrix. The "least squares" mean (LS mean) estimates of treatment differences and their 95% CIs will be presented for each time point. In addition, a p-value will be presented for the primary comparisons. The LS mean change from baseline to each post-baseline will be plotted by treatment group. To examine the pattern of missing data, the number and percentage of subjects with a mean MADRS score will be presented by treatment group. Summary statistics for MADRS score and change from baseline will also be presented, based on observed scores (no imputation of missing data) calculated from all available data. These summaries will also be produced for the subset of subjects who have a non-missing MADRS score.

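### SAP 5.5 starts the MADRS-S and SDS models from an unstructured covariance over 14 or more visits in about 30 patients; the fit is fragile to missed forms, and a smaller baseline-adjusted model would be safer

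*Protocol*

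**What the plan says.** SAP 5.5 puts the change-score endpoints for MADRS, MADRS-S, SDS and CGI into MMRMs with treatment, timepoint and their interaction, and states: "The models will be built as of the primary endpoint (see 5.4 Primary analysis". SAP 5.4 says of that model: "An unstructured covariance matrix will be used to estimate the within subject variation". It adds Kenward-Roger degrees of freedom and a fallback: "If this analysis fails to converge, the following structures will be used in order: heterogeneous Toeplitz (TOEPH), Antependence (ANTE1), heterogeneous autoregressive (ARH1", followed by AR(1) and compound symmetry. The selection rule is: "The first covariance structure yielding convergence will be used". Any structured matrix is paired with sandwich standard errors. The listed model terms do not include the baseline score.

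The self-ratings are frequent. Protocol 5.5.2 has SDS "collected electronically at day -3, 0, 8, 15, 42 and then monthly until 365". Protocol 5.5.1.1 has MADRS-S before dosing "and day 1-8, 15 and monthly from day 42, 180 and 365 electronically". The named secondary endpoints for both scales (SAP 3.2) are the change to Day 365 and the change to the average over Days 8 to 365.

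Protocol 16.4.1 prescribes a baseline-adjusted ANCOVA for the primary endpoint and adds: "The same method will be applied for all other single measure endpoints". Multiple-measurement endpoints go to MMRM there, with no covariance structure named.

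**The concern.** An unstructured matrix is a reasonable default for the rater MADRS, which has four or five post-dose visits. SAP 5.5 carries it without adaptation to scales rated 14 to 21 times after dosing, in the same 30 or so patients. The number of variances and covariances then far exceeds the number of patients. The forms are completed online over a year, so some will probably be missed.

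Four named secondary endpoints depend on this: Day 365 and the period mean, for each of MADRS-S and SDS. Two things could go wrong:

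- A nearly singular fit may formally converge and be reported, with a model-based standard error that is too small. The sandwich estimator applies only to structured matrices, so it would not be used.
- If the fit does not converge, the first replacement ties correlation to visit order and not to elapsed time.

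**Working it through.** **Inputs.** About 30 patients, 15 per arm (SAP 5.1). That figure reproduces: with a difference of 11, SD 10 and a two-sided 5% t-test, 14 per arm gives 79.99% power and 15 gives 82.8%. It is used here only as the number of patients.

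Post-dose times from Protocol Table 1 and sections 5.5.1.1 and 5.5.2:

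- SDS: Days 8 and 15, plus 12 columns (42, 72, 102, 132, 162, 192, 223, 253, 283, 313, 343, 365) = 14.
- MADRS-S: the same 14 plus Days 1-7 = 21. The named Day 8-365 endpoint needs only the 14.

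**Covariance parameters for p visits.**

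| Structure | Formula | p = 14 | p = 21 |
|---|---|---|---|
| Unstructured | p(p+1)/2 | 14×15/2 = 105 | 21×22/2 = 231 |
| TOEPH, ANTE(1) | 2p−1 | 27 | 41 |
| ARH(1) | p+1 | 15 | 22 |
| AR(1), CS | 2 | 2 | 2 |

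For comparison, four or five rater-MADRS visits need 4×5/2 = 10 or 5×6/2 = 15.

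**Can the unstructured matrix be estimated?** With complete data there are 30 − 2 = 28 residual degrees of freedom, above both 14 and 21, so the estimate exists. With gaps, a sufficient condition is at least p + 2 patients with every form: 16 for p = 14 and 23 for p = 21. At an assumed 5% of forms missed independently:

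- p = 14: 0.95^14 = 0.49, about 15 complete patients expected; the chance of 16 or more is 0.38.
- p = 21: 0.95^21 = 0.34, about 10 expected; the chance of 23 or more is about 0.

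**Simulated REML fits.** These used 15 per arm and arm-by-visit means. Two correlation patterns were assumed: 0.5 + 0.5×0.6^lag, and 0.4-0.9 falling with the time gap. Failure means a singular estimate or, in one set of runs, also no convergence at the iteration limit. Most scenarios had 20-100 fits.

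| Scenario | 14 visits | 21 visits |
|---|---|---|
| Complete data | 0 of 60 | 0 of 60 |
| 20% monotone dropout only | 0 of 60 | about 18% of 33 |
| 1% missed forms | 0 of 60 | about 2% of 60 |
| 2% missed | 0 of 60 | 68% of 25 |
| 3% missed | not run | 23 of 25 |
| 5% missed | about 11-20% | 100% |
| 5% missed + 10% dropout | 34%; 15 of 40 | not run |
| 10% missed | 88-100% | 100% |

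A small run of 10 fits that counted only the eigenvalue criterion gave 7 of 10 at 14 visits and 10% missed. A five-visit model was singular in 0 of 100 trials even with 20% dropout plus 10% missed forms.

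**Consequence at Day 365.** At 14 visits without dropout, type I error stayed near nominal. With 20% dropout plus 5-10% missed forms, the average model-based standard error was about 4.0 against an empirical 4.4 to 4.8. The shortfall is 1 − 4.0/4.4 = 9% to 1 − 4.0/4.8 = 17% on these rounded values. The estimate was also about 8% less precise than a five-visit fit or a simple Day 365 comparison. The Kenward-Roger adjustment was not simulated.

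**Fallback.** TOEPH gives one correlation to every pair of adjacent visits. Those gaps are 15 − 8 = 7 days, 42 − 15 = 27, mostly 30, up to 223 − 192 = 31, and 1 day within Days 1-8 of MADRS-S. ARH(1) and AR(1) share this property. ANTE(1) does not, but it stands behind TOEPH in a list where the first structure to converge is taken.

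**The case against.** The strongest reply is that SAP 5.4 anticipates failure. The sentence that imports the unstructured start also imports an ordered fallback, a fixed selection rule and sandwich errors for any structured matrix. In spot checks at 10% missed forms (three data sets per visit count), ARH(1) and CS gave non-singular fits every time. That stands: a reader might infer from 105 or 231 parameters that the analysis is left without a model, or that the choice is unplanned, and neither is so. The reply does not cover a near-singular unstructured fit that converges, because non-convergence is the only exit. Nor do sandwich errors protect the point estimate, which depends on the covariance model when data are incomplete.

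A second reply concerns the visit counts. SAP 5.5 lists no visit set, so 21 is a maximum for MADRS-S. For SDS, Protocol 9.7 names only MADRS-S and EQ-5D as monthly, and the functional-disability item in SAP 3.3 uses four post-dose days (10 parameters). Both observations are fair. Still, Protocol 5.5.2 and Table 1 do schedule SDS monthly, and the named period mean covers 14 scheduled times on either scale.

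A third reply is that the missed-form rates and correlations are assumptions. That is correct, and the size below is conditional on them.

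**Conclusion.** The point holds as a modest weakness in the model for four secondary endpoints. The unstructured start asks for 105 covariance parameters (up to 231) from about 30 patients. It works with complete data. At 14 visits it also works with dropout alone. At 14 visits it becomes singular in about 10-20% of trials at 5% missed forms and in about 90% or more at 10%; at 21 visits it fails in most trials at 2-3%. With about 20% dropout plus missed forms, the Day 365 standard error is roughly 10-15% too small and precision is somewhat lower than with a smaller model.

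Two stronger readings are not supported. One is that the model usually cannot be estimated: that would need a missed-form rate, which the documents do not give. The other is that its standard errors are meaningless: type I error was near nominal without dropout, and in one set of runs the non-singular fits had average model-based standard errors at or above the empirical ones (3.6 against 3.1; 4.0 against 3.8).

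The results rest on assumed correlations and missingness, modest simulation sizes and model-based standard errors without Kenward-Roger. The SAP leaves these endpoints unadjusted for multiplicity and treats them as exploratory. The primary rater-MADRS model is not affected.

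**What to change.** In SAP 5.5, for MADRS-S and SDS:

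- Estimate the Day 365 change from an MMRM limited to Days 8, 15, 42, 192 and 365, with the baseline score as covariate. Five visits need 15 covariance parameters. Day 192 is the Table 1 column closest to Day 180.
- Analyse each patient's mean of the available Day 8-365 scores with the baseline-adjusted ANCOVA of Protocol 16.4.1.
- If a model over all visits is kept, name the visit set and start from ANTE(1), or from a structure based on actual days such as spatial power, and not from unstructured or TOEPH.

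The cost is SAP wording only, with no change to design or data collection. There are two downsides. The other monthly scores then enter only through the patient mean or descriptively. The patient mean averages whatever forms were returned, so the SAP should say that this is intended.

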Placebo-controlled studies of psilocybin to treat depression have only been conducted in patients with cancer, not in medically-healthy patients. And the single 12 participant study conducted to date of psilocybin intervention in medically-healthy patients with TRD was not blinded and did not include a placebo condition. The scientific rationale for the current study is thus to address both these methodological gaps in understanding the potential value of single dose psilocybin for MDD in medically-healthy patients, and, importantly, explore the biological underpinning of this effect. Specifically, this study will address this by: 1) randomizing a population of medically-healthy participants with MDD; 2) utilizing a randomized, double-blind, placebo-controlled, parallel-group design to control for baseline covariates, placebo and other therapeutic effects not specifically linked to medication exposure; and 3) utilizing PET and the radioligand [C]UCB-J to test the hypothesis that successful psilocybin treatment of MDD is associated with increased synaptic density in MDD relevant brain regions, analysis of peripheral blood mononuclear cells (PBMCs), plasma and CSF with regards to potential biomarkers of MDD and psilocybin response can be used, and a MRI paradigm to explore associations between treatment expectation and CNS metabolic consequences of treatment.

In addition and of importance, data derived from this study will allow for a refinement of effect size estimates for larger phase 3 studies of single dose psilocybin in MDD. Moreover, because previous psilocybin studies utilized weight-based dosing, the current study will allow us to examine whether fixed-dose psilocybin will produce effect size benefits consistent with those seen with weight-based dosing.

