## 4. Study Design

Thirty patients (males and females) ages 20 to 65 who, at Screening, meet ICD-10 criteria for recurrent MDD with a current depressive episode of at least a 30-day duration, an on-site Screening MADRS score 22 (consistent with moderate or greater depressive symptom severity), 30% symptom decrease from web-screen, and who meet all other inclusion/exclusion criteria at Baseline will be enrolled into the study and randomized with a 1-to-1 allocation under double-blind conditions to receive a single 25 mg oral dose of psilocybin or a single 100 mg oral dose of niacin. Expecting a maximum of 20% drop out rate a maximum of 6 more subjects may be randomized, in order to reach 30 patients completed (performed all study related activities up until and including PET#2 day 15). Niacin will serve as an active placebo that provides an acute physiological response (flushing) that may aid in blinding of intervention allocation. All randomized participants will be included in the Full Analysis Set (FAS) that will be used for analyzing primary and secondary study endpoints.

Randomization will occur for participants who have been determined to be eligible for the study and will occur the morning prior to dosing. Following this, participants will be randomized to one of two intervention groups. Participants are randomized in blocks in a 1:1 ratio in a blinded fashion to the psilocybin group or the active control group. The block size will not be shared. Randomization will be done at the site by strictly following a randomization list in sequential order. If a patient is replaced the new patient will be allocated a randomization number with the same treatment while keeping the double blinded allocation. This will be performed by having back-up blinded treatment allocations for each subject in sealed envelopes. These will only be used and opened following withdrawal. Importantly, the allocated treatment will remain blinded for both the withdrawn and replacement subject as well as for the study team.

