## 5. Statistical analysis

### 5.1. Power analysis and Sample Size Determination

The difference between psilocybin and placebo in change from baseline to Day 8 in MADRS total score (primary endpoint) will be analyzed for the Full Analysis Set using Analysis of Covariance including treatment as main effect and baseline as covariate.

Based on prior controlled studies of psilocybin in cancer- related depression and anxiety, a decrease in depression symptoms from baseline to one-week post-dose of at least 30% is expected in the placebo

arm. In an open-label study of psilocybin the change in MADRS total score from baseline to 1 week was -23.3. Several clinical studies in the literature report a standard deviation in change in MADRS total score around 10.

A sample size of 15 in each group will have 80% power to detect a difference in means of 11 (the difference between a psilocybin mean, of -23 and a placebo mean, of -12) assuming that the common standard deviation is 10 using a two group t-test with a 5% two sided significance level.

Considering the short duration between treatment and primary endpoint measurement day 8 the risk of withdrawal is considered low. The total sample size is set to 30 patients completing day 15. In case of withdrawals before day 15 additional patients may be randomized to ensure 30 patients included in the primary and secondary analyses. Estimating a maximum of 20% withdrawals, a maximum of 6 additional subjects can be included.

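### SAP 5.5 assigns a paired t-test to comparisons between two independent arms; the error is confined to supplementary visit-wise tests and one sentence corrects it

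*Protocol*

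**What the plan says.** SAP section 5.5 first assigns MMRM models to the MADRS, MADRS-S, SDS and CGI secondary endpoints, built like the model in SAP 5.4. It then adds: "Paired t-test will be performed for between-groups comparisons at all time points, and between all time points over time against baseline". One test thus gets two jobs: comparing the arms, and comparing later visits with baseline.

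The design is described consistently as two separate groups:

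- Protocol 4.4.3 describes the trial as "utilizing a randomized, double-blind, placebo-controlled, parallel-group design".
- SAP section 4 says "Participants are randomized in blocks in a 1:1 ratio in a blinded fashion to the psilocybin group or the active control group". Neither document describes matching or crossover.
- SAP 5.1 bases the sample size on an independent-groups comparison, "using a two group t-test with a 5% two sided significance level".
- Protocol 16.4.1 gives the method for repeated endpoints as "Treatment differences of multiple measurement endpoints will be analyzed by the mixed model repeated measurements analysis (MMRM) method" and mentions no paired test.

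**The concern.** A paired t-test needs a natural partner for each observation. A patient's own baseline is such a partner; a different patient in the other arm is not. Randomisation blocks do not supply one-to-one partners across arms. The replacement rule does not either, because a replacement receives the same treatment as the patient who left and so links patients within an arm.

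To run the test as written, an analyst would have to line up the two arms in some order that the SAP does not state. Two analysts using different sort orders would report different p-values from the same data. If the numbers observed at a visit differ between arms, some patients must be dropped for the test to run at all. The SAP also does not say which result governs if the paired test and the MMRM contrast disagree for the same score and visit.

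**Working it through.** **Inputs.** From SAP 5.1: "A sample size of 15 in each group will have 80% power to detect a difference in means of 11", "assuming that the common standard deviation is 10", two-sided 5%, and "Estimating a maximum of 20% withdrawals, a maximum of 6 additional subjects can be included". From Protocol 16.4.3: missing values are in general not imputed.

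**1. The plan's own figure.** For two independent groups:

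- Standard error = 10 × √(2/15) = 3.65.
- Noncentrality = 11/3.65 = 3.01, with 28 degrees of freedom and critical t 2.048.
- Power from the noncentral t is 82.8% at 15 per arm (80.0% at 14 per arm).

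The stated 15 per arm for 80% power is reproduced, slightly on the conservative side.

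**2. What arbitrary pairing changes.** With complete data, the mean difference is the same under every pairing. The estimated standard error is not: the variance of the paired differences is s₁² + s₂² − 2·s₁₂, and the sample covariance s₁₂ depends only on who was lined up with whom. For independent arms its expected value is zero, so on average nothing is gained, while the degrees of freedom fall from 28 to 14 and the critical t rises from 2.048 to 2.145. Noncentrality stays at 3.01, so power at a difference of 11 is 80.0% instead of 82.8%.

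**3. How far p can move in one dataset (simulated, 15 per arm, SD 10 in each arm, 20,000 random re-pairings).**

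| Observed difference | Independent p | Paired p, range | Pairings with p < 0.05 |
|---|---|---|---|
| 7.5 | 0.049 | 0.00007 to 0.148 (central 95%: 0.011 to 0.117) | 38% |
| 11 | 0.0054 | 0.000002 to 0.039 | 100% of those sampled |

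The first row was deliberately placed at the significance border.

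**4. How often one arbitrary pairing changes the verdict (200,000 simulated trials per row, normal data).**

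| True difference | Verdicts differ | Significant on independent test only | Significant on paired test only |
|---|---|---|---|
| 0 | 2.4% | 1.2% | 1.2% |
| 8 | 9.0% | 5.9% | 3.0% |
| 11 | 6.4% | 4.6% | 1.8% |

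Under no difference the paired test rejects in 5.0 to 5.1% of trials, so its average error rate is correct. At 11 the net loss, 4.6% − 1.8% = 2.8 points, matches the power difference in step 2 (82.8% − 80.0%).

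**5. Missing visits.** If two patients per arm miss a visit at random, the independent test still uses 13 + 13 = 26 patients. If pairs were fixed beforehand, the expected number of complete pairs is 15 × (13/15)² = 11.3, or about 22.5 patients.

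**The case against.** The strongest reply is that nothing important rests on this test. The primary MADRS comparison is an MMRM in SAP 5.4, with treatment differences and confidence intervals at each time point. The same type of model covers MADRS, MADRS-S, SDS and CGI in SAP 5.5, just before the sentence at issue. The t-tests are additional, sit under the heading of sensitivity analysis, and belong to a plan that makes no multiplicity adjustment and asks for exploratory interpretation (SAP 5.2). The sentence also looks like two tasks merged in drafting, since SAP 5.1 uses a two-group t-test and SAP 5.3 an unqualified t-test for group differences. A programmer would probably notice that no pairing variable exists.

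Most of this stands, and it limits the severity. It does not make the sentence right: the SAP prescribes the test explicitly, and an analyst following it literally would produce output that nobody could reproduce.

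Three stronger readings are tempting and are not supported:

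- *All between-group p-values for these scores are arbitrary.* This is true only of the paired test; each score also has an MMRM contrast.
- *The false-positive rate is inflated, or one arm is favoured.* Step 4 shows neither.
- *The verdict is unstable in a third to a half of trials.* Such figures arise by asking whether any of 100 re-pairings disagrees with another: 17%, 47% and 33% at differences of 0, 8 and 11. They grow with the number of pairings tried; at a difference of 8 the share is 11% with 2 pairings, 31% with 10, 46% with 100 (a separate run) and 56% with 1000. An analyst would run one pairing, so the relevant figures are those in step 4.

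**Conclusion.** The between-group half of the sentence in SAP 5.5 is wrong as written. The arms are independent, no pairs exist, and it conflicts with the SAP's own sample-size section. The defect is a p-value that depends on an unstated ordering, the halving of the degrees of freedom, and the loss of patients when numbers are unequal. One arbitrary pairing gives a different verdict from the independent test in about 2% of trials with no difference, 9% at a difference of 8 and 6 to 7% at 11. Average type I error is preserved, and the power loss at 11 is about 3 points.

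These sizes assume normal data, 15 complete patients per arm and a common SD of 10, which the SAP gives for MADRS change only. For the other scales, read the differences as 0, 0.8 and 1.1 standard deviations.

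The harm is confined to supplementary visit-wise tests; the primary analysis and the MMRM results for the secondary scores are not affected. It should be fixed, but it is not a fatal flaw.

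**What to change.** Replace the sentence in SAP 5.5 with two. First: between-group comparisons at each time point use an independent two-sample t-test, supplementary to the MMRM visit contrasts already specified. Second: paired t-tests are used only for change from baseline within each arm, and are labelled descriptive because they do not estimate the treatment effect.

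The new text should not call those contrasts baseline-adjusted. The MMRM in SAP 5.4 and 5.5 lists treatment, timepoint and their interaction, with no baseline covariate; adding one would be a separate change to the model.

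The cost is one sentence of SAP text, with no effect on sample size, data collection or the main models. It is best made before unblinding, so that the choice of test cannot be seen as driven by the data.
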